## Background

Essential hypertension continues to be an important public-health challenge worldwide [1]. Hypertension is an independent risk factor for premature death, heart disease, stroke, peripheral vascular disease, and renal failure. Hypertension affects 29.3% of the adult population in the United States [2]. In 2009,the direct and indirect costs for hypertension in the United States are projected to be approximately $73.4 billion [3]. In the fourth National Nutrition and Health Survey in 2002, the prevalence of hypertension among Chinese population was 18.8% [4], affecting approximately 200 million individuals in China, while mild hypertension accounts for >60% [5]. Furthermore, the number of hypertensive patients is still increasing [6]. It is also reported that in China, the direct medical costs for hypertensive patientsaged 35 to 75 years are ¥20.2 billion [7].

Pharmacological treatment remains the chief treatment option for mild hypertension. However, a recent Cochrane review found that there is no proved benefit in antihypertensive drugs treatment for patients with mild hypertension. In addition, owing to adverse effects of antihypertensive drugs, 9% of patients discontinue their treatment [8]. Non-pharmacological interventions including acupuncture prevail as a treatment option for hypertensive patients [9]. In China, acupuncture has been used to treat disease for >2,500 years, and it is also widely used all around the world. Nowadays, acupuncture is used to treat cardiovascular disease (such as angina pectoris [10], hypertension [11]). Several randomized controlled trials of acupuncture to treat hypertension had been conducted, but the results were not consistent. Therefore, we designed a multicenter randomized controlled trial to confirm whether acupuncture is efficacious and safe for hypertension.

In this trial, we first intend to investigate the efficacy of acupuncture to lower the blood pressure comparing the waiting-list control and invasive sham acupuncture groups. Second, we attempt to determine whether there is a difference between acupoints on the affected meridians according to meridian syndrome differentiation and the acupoints on the non-affected meridians. This clinical trial is financed by the national basic research program (973program) in China, and is registered with an identifier (http://NCT01701726) by clinicaltrials.gov in the USA.

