Before randomization, all participants will undergo routine tests of blood, urine, stool sample, electrocardiogram examination, Doppler echocardiography, carotid ultrasonography, as well as blood biochemical tests (AST, ALT, BUN, Scr, fasting glucose, triglyceride, HDL cholesterol, LDL cholesterol, albumin/creatinine.). These tests will help identify and exclude participants with serious illnesses of the heart, liver, and kidneys, or other severe diseases.

Adverse events are defined as any unexpected or uncomfortable signs, symptoms, or diseases, regardless of the intervention. These adverse events include bleeding, hematoma, fainting, serious pain, and local infection. If any adverse events happen during the entire observation period, all the details should be documented in the case report form.

We have designed a case reported form containing a variety of information, and this will be completed by the corresponding researchers at each center. At each center, the obtained information will be recorded on an electronic database, for subsequent statistical analysis. During the observation period, if there are any drop-outs or withdrawals, the investigator must find out their reasons and record them in the case report form. The patients’ compliance during the 6 weeks of treatment and 6 weeks of follow-up will also be documented.

#### **
*Sample size calculation and statistical analysis*
**

According to the previous literature [26], the average 24-hSBP of hypertensive patients rose 1.6 mmHg after being treated by sham acupuncture, while the average 24-hSBP of hypertensive patients lowered 5.4 mmHg after being treated with verum acupuncture. Therefore, the adjusted mean difference between the two groups was 7 mmHg. In this study, we anticipated an 12 mmHg improvement by affected meridian acupuncture; 10 mmHg by non-affected meridian acupuncture; 3 mmHg by sham acupuncture; and 0 mmHg in the waiting-list group. The standard deviation is set as 20. We calculated this using 90% power at a 5% significance level with G*Power (version 3.1.2, Franz Faul, Universität Kiel, Germany), and the result showed an estimated 93 patients per group. Considering a drop-out rate of 15%, we plan to enroll 107 patients per group, 428 patients in total for the four different groups.

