Design highlights: first, unlike previous trials, we only include mild hypertensive patients without serious complications as it is safe for all subjects to go off hypertensive drugs and only be treated with acupuncture. We also rule out the influence from hypertensive drugs. Besides, by focusing on mild hypertension [33], we can cut down the compounding effect from different severities of hypertension. Second, we use electro-stimulation in the acupuncture groups aiming to ensure the stimulations between groups and individualsare equal. Third, in order to ensure the quality of this trial, we require that all the participating acupuncturists have at least 5 years of training and 5 years of practical experience. Before the trial, they will take a training course which includes the study protocol, methods for acupuncture treatment, and operating demonstration for this trial. After the course, they need to take an exam about the training course to be qualified for this trial. Meanwhile, we will designate special clinical monitors to check the progress of the trial and audit the accuracy and validity of the original data at each participating hospital once a month. Fourth, in our trial, a first ever large sample of patients will be recruited, which will make the results more powerful and convincing. Moreover, our design has a good understanding of theory of TCM and acupuncture.

One important limitation that may be present in this study is that it is an open-label trial. We design a waiting-list group as a blank controlled group. It is impossible to execute a blinding method. In order to overcome this problem, the acupuncturist and the outcome assessors are different, with respect to making the outcome assessment objectively. We also prevent the investigators and statisticians from randomization, to make sure all of them are blind to allocation. Among the three acupuncture groups, we conceal the patients from assignation so the patients do not know which acupuncture group they are allocated in.

This is a large scale, multicenter, randomized, controlled trial, and utilizes high quality methodologies. It may provide evidence for the effectiveness of acupuncture as a treatment for mild hypertension and confirm the existence of special effect of acupoints on affected meridians based on meridian syndrome differentiation.

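### The single 90% power figure names no contrast and cannot cover affected versus non-affected meridian acupuncture, where the protocol's own assumptions give about 10%

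*Protocol article*

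**What the plan says.** All the planning inputs are in Methods/Design, under the heading Sample size calculation and statistical analysis. The anticipated falls in 24-h SBP are: "we anticipated an 12 mmHg improvement by affected meridian acupuncture; 10 mmHg by non-affected meridian acupuncture; 3 mmHg by sham acupuncture". For the waiting list no change (0 mmHg) is assumed. On variability: "The standard deviation is set as 20". The size was obtained "using 90% power at a 5% significance level with G*Power", and "the result showed an estimated 93 patients per group". Then: "Considering a drop-out rate of 15%, we plan to enroll 107 patients per group". The paragraph does not say which comparison the 90% refers to, or whether the test is one- or two-sided.

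The same section lists three comparisons on the primary outcome: pooled acupuncture against waiting list, pooled acupuncture against sham, and a comparison between acupuncture groups. All use ANCOVA with Bonferroni adjustment. Analyses are by intention to treat and per protocol, with last observation carried forward.

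Affected versus non-affected meridians is a main question. The Background gives it as the second aim: "we attempt to determine whether there is a difference between acupoints on the affected meridians" and those on non-affected meridians. The Discussion returns to it and closes by saying that the trial may "confirm the existence of special effect of acupoints on affected meridians based on meridian syndrome differentiation". The protocol does not call the contrast exploratory, and it does not restrict the 90% to other contrasts.

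**The concern.** A single power figure placed directly after four assumed arm means invites the reader to apply it to every comparison the trial lists. For the affected versus non-affected contrast, the assumed means are only a tenth of an SD apart, while the group size is under 100.

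Two things are at stake. First, if the sponsor's hypothesis is exactly right, the test will miss it about nine times in ten. Second, a reader who relies on the stated 90% could take that miss as evidence that point selection does not matter, which a trial of this size could not show.

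**Working it through.** **The plan's own figure.** I could not reproduce 93 per group from any coherent reading of the stated inputs.
- Four-arm ANOVA (means 12, 10, 3, 0; SD 20; f = 0.246): 60 per group for 90% power. With 93 per group the power is 98.6%.
- Two-sided 1:1 t-tests at 0.05 and 90% power: 173 per group for 7 mmHg, 105 for 9, 86 for 10 and 60 for 12.
- Two active arms pooled against sham (8 mmHg, 2:1): 100 per single arm.

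The step to 107 is 93 × 1.15 = 106.95. So the calculation does not reveal which contrast was meant. What follows does not depend on that.

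**Inputs for affected versus non-affected.** Difference δ = 12 - 10 = 2 mmHg; SD σ = 20; n = 93 per group (the plan's evaluable number) or 107 (everyone enrolled, as ITT with LOCF could retain).

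**Power.** SE = σ√(2/n); power ≈ Φ(δ/SE - z), with z = 1.960 at two-sided 0.05 and z = 2.394 at 0.05/3. The divisor of 3 is my assumption, taken from the three listed comparisons.

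| n per group | SE | δ/SE | Power, 0.05 | Power, 0.05/3 |
|---|---|---|---|---|
| 93 | 2.933 | 0.682 | Φ(-1.278) = 10.1% | Φ(-1.712) = 4.3% |
| 107 | 2.734 | 0.731 | Φ(-1.229) = 11.0% | Φ(-1.663) = 4.8% |

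The exact noncentral t gives 10.4% and 4.4% at 93, and 11.3% and 4.9% at 107. Bonferroni over all six pairwise tests would give 2.5% at 93.

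**More favourable readings, n = 93.**
- One-sided 5%: Φ(0.682 - 1.645) = 17%.
- ANCOVA, if 20 is the SD before baseline adjustment. The residual SD is 20√(1 - ρ²), and ρ is assumed because the protocol gives none. ρ = 0.5, 0.7 or 0.8 gives a residual SD of 17.3, 14.3 or 12.0, and power of 12%, 16% or 20% at 0.05 (5%, 7% or 10% at 0.05/3).
- All of these together, with 107 per group: SE = 12√(2/107) = 1.641; Φ(2/1.641 - 1.645) = Φ(-0.426) = 34%.

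**Difference detectable with 90% power at two-sided 0.05.** (1.960 + 1.282) × SE = 9.5 mmHg at 93 and 8.9 mmHg at 107. These are 4.8 and 4.4 times the assumed 2 mmHg.

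**Size needed for 2 mmHg.** n = 2(1.960 + 1.282)²/0.1² ≈ 2,102 per group; with z = 2.394, about 2,702.

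**Precision.** Unadjusted 95% CI half-width, t quantile × SE: 1.973 × 2.933 = 5.8 mmHg at 93 and 1.971 × 2.734 = 5.4 mmHg at 107.

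**The other contrasts.** With 93 per arm and the two active arms pooled, SE = 20√(1/186 + 1/93) = 2.540. Against waiting list (11 mmHg), power is 99% at 0.05 and 97% at 0.05/3. Against sham (8 mmHg), it is 88% and 77%. The shortfall is greatest by far for affected versus non-affected.

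**The case against.** The strongest reply is that the protocol never claims 90% power for this contrast. The sample size paragraph opens with a cited verum versus sham difference of 7 mmHg, which suggests that efficacy drove the sizing. A reader might infer a false power claim about affected versus non-affected meridians, and the text does not support that. What stands is that the figure carries no scope, sits beside the 12 and 10 mmHg assumptions, and cannot apply to one of the two stated aims.

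A reader might also infer that the trial promises to settle the question. The Background speaks of an attempt to determine a difference, and the closing Discussion sentence is governed by *may*. That is softer than a promise, although *confirm* is still more than about 10% power can bear.

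The 4-5% figure should not be quoted as the protocol's own. The number of Bonferroni tests is not given. The Abstract counts sham among three acupuncture groups, so the comparison between acupuncture groups may be more than one test. The primary endpoint paragraph names DBP as well as SBP. Nor is 91 per group (107 less 15%) the planned analysis set, since ITT with LOCF can keep up to 107.

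Sidedness and baseline adjustment are open too, and both can raise power. None of these points brings it near 90%. Finally, nothing in the protocol says that a null result would be read as equivalence. That is a risk for readers, not a stated intention.

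**Conclusion.** The concern holds as a defect of scope with a large numerical consequence. The unqualified 90% cannot apply to affected versus non-affected meridian acupuncture. On the protocol's own 2 mmHg and SD of 20, two-sided power at 0.05 is about 10-11% (93 to 107 per group). It is about 4-5% under an assumed three-way Bonferroni split, and about 17-20% at 93 per group with one-sided testing or with ANCOVA at an assumed baseline correlation of up to 0.8. Even these concessions combined, at 107 per group, reach only 34%. The low power rests on stated inputs; the spread comes from the unstated alpha split, sidedness and meaning of the SD. That affected versus non-affected falls under the third listed comparison is the natural reading, not an explicit statement. The efficacy contrasts are much better placed and are not the subject of this point.

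**What to change.** In the sample size paragraph:
- Name the contrast that the 90% refers to, and say that it does not apply to affected versus non-affected meridians.
- Give that contrast's own power, showing the alpha, the sidedness and whether the SD of 20 is before or after baseline adjustment.

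In the analysis paragraph:
- Report the contrast as an estimate with a 95% CI. The expected unadjusted half-width is about 5.4 to 5.8 mmHg; ANCOVA may narrow it.
- State that a non-significant result will not be read as showing that the two point sets are equivalent.

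In the Discussion, soften the sentence about confirming a special effect of affected-meridian points to match.

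Taking the contrast out of the Bonferroni family is optional. It would leave more alpha for the efficacy comparisons, but it demotes one of two stated aims in a trial that had already recruited 184 participants. Keeping it in with its power disclosed is also acceptable.

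The required changes are wording and need no extra patients. The cost is a less favourable stated power for one aim.

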### Randomization

Randomization is conducted by the third party (the Brightech Magnsoft Data Services Company) using text messages or a website. If the randomization succeeds, the investigators will receive an email confirmation. The randomization sequence (blocked, stratified for centers) is generated through the randomization module of the synthesized management platform of the Brightech Magnsoft Data Services Company (block length is unknown to centers). This procedure ensures each eligible patient having an equal probability of being assigned to four different groups, which will not be influenced by the researchers.

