Statistical analysis protocol was designed by the Brightech-Magnsoft Data Services Company and principal investigators. Analysis of all data in this trial will be performed by the Brightech-Magnsoft Data Services Company. The data will be analyzed with SAS 9.1 and SPSS13.0 software packages. All analyses will be on the basis of the intention-to-treat (ITT) population and per-protocol (PP) population. The result of the ITT analysis will be compared with that of the PP analysis to determine whether the results are consistent. Missing data will be filled by Last Observation Carry Forward rules.

Demographic characteristics and other baseline values will be described using descriptive statistics for each group. For the primary outcome, we will run a comparison between pooled acupuncture groups and waiting list control group to figure out whether acupuncture is more effective for this condition. We will then run another comparison between the pooled acupuncture groups and sham acupuncture group to find out whether acupuncture is more efficacious. Finally, a comparison between acupuncture groups will be run to see if selecting points along meridians was a better treatment option. The above analysis will be performed using the ANCOVA model. Multiple comparisons will be adjusted according to the Bonferroni correction method.

The repeated measures analysis will be used in the different time point assessments for the secondary outcomes. The Kruskal-Wallis test will be employed in the analysis of skewed distribution data. There is a designated acupuncturist in each center to all the acupuncture treatment, which probably introduces clustering effect in this trial. Therefore, we calculated the intra-cluster correlation coefficient from the results of this trial and report the coefficient.

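### The stated 93 per group at 90% power and a 5% level matches none of the planned comparisons and makes no allowance for the planned Bonferroni correction

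*Protocol article*

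**What the plan says.** All but one of these statements are in the protocol article under Sample size calculation and statistical analysis.

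- **Effects:** "we anticipated an 12 mmHg improvement by affected meridian acupuncture", followed by "10 mmHg by non-affected meridian acupuncture; 3 mmHg by sham acupuncture; and 0 mmHg in the waiting-list group".
- **Spread:** "The standard deviation is set as 20". The text does not say whether this is the SD of a single reading, of the change, or of the ANCOVA residual.
- **Error rates and result:** "We calculated this using 90% power at a 5% significance level", and "the result showed an estimated 93 patients per group". The test or contrast that was powered is not named, nor is the sidedness.
- **Enrolment:** "Considering a drop-out rate of 15%, we plan to enroll 107 patients per group, 428 patients in total".
- **Analysis of the primary outcome:** three ANCOVA comparisons are listed in order. They are pooled acupuncture versus waiting list, pooled acupuncture versus sham, and one acupuncture group versus another (read here as affected versus non-affected meridian). Then: "Multiple comparisons will be adjusted according to the Bonferroni correction method". No divisor is given.

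Under Randomization, allocation is equal ("each eligible patient having an equal probability of being assigned to four different groups"), so two pooled verum arms face one control arm at 2:1.

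**The concern.** The article gives both a design power and an analysis, and the two do not fit together. The size is computed at 5%, while the analysis tests each of several comparisons at a Bonferroni-reduced level. Since no contrast is named, a reader will take the 90% to apply to the comparisons listed in the next paragraphs.

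That affects interpretation. The sham comparison is the one the article uses to judge whether acupuncture is more efficacious. The comparison of affected with non-affected meridians carries the point-specificity hypothesis in the Discussion. A null result on either would be given more weight than the design supports if a reader believed that each had 90% power.

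**Working it through.** **Inputs.** AMA (affected meridian) 12, NMA (non-affected meridian) 10, sham 3, waiting list 0 mmHg; SD 20; power 90%; level 5%, taken as two-sided; equal allocation. Mean of AMA and NMA = 11. Differences:

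- pooled AMA+NMA v waiting list: 11 − 0 = 11, at 2:1
- the same with sham also pooled: (12 + 10 + 3)/3 = 8.33, at 3:1
- pooled AMA+NMA v sham: 11 − 3 = 8, at 2:1
- AMA v NMA: 12 − 10 = 2, at 1:1

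**Step 1: try to reproduce 93.** With r patients on the pooled side per control patient, the normal approximation is

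n per group = (1 + 1/r) × [(z₁₋α/₂ + z_power) × SD / difference]².

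For pooled v sham: 1.5 × [(1.960 + 1.282) × 20/8]² = 98.5, so 99 (100 with the noncentral t).

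| Comparison | n per group, two-sided 5%, 90% power (noncentral t or F) |
|---|---|
| Pooled AMA+NMA v waiting list | 53 |
| Pooled including sham v waiting list | 82 |
| Pooled AMA+NMA v sham | 100 |
| AMA v NMA | 2,103 |
| Four-group ANOVA | 60 |

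Single-arm pairs do not give 93 either: AMA v waiting list 60, NMA v waiting list 86, AMA v sham 105, NMA v sham 173. One-sided 5% gives 81 for pooled v sham. The figure is not reproduced.

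**Step 2: how far off is 93 without adjustment?** For pooled v sham at two-sided 5%, 93 per group gives 88%. That is close to 90%.

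**Step 3: completers.** 93 × 1.15 = 106.95, which explains the 107. But 107 × 0.85 = 90.95, so 15% drop-out leaves about 91 per group.

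**Step 4: apply Bonferroni.** Assume a divisor of 3 (three listed comparisons), so α = 0.05/3 = 0.0167 and z = 2.394. Take SD 20 as the ANCOVA residual SD and 91 per group.

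Pooled v sham: SE = 20 × √(1/182 + 1/91) = 2.568; 8/2.568 = 3.116; 3.116 − 2.394 = 0.722; power about 76.5% (76.0% with the noncentral t).

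| Comparison | Power at 0.0167, 91 per group |
|---|---|
| Pooled AMA+NMA v waiting list | 97% |
| Pooled including sham v waiting list | 85% |
| Pooled AMA+NMA v sham | 76% |
| AMA v NMA | 4% (10% even at 5%) |

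**Step 5: vary the assumptions for pooled v sham.** The document fixes none of these, so they are shown as a range. Each row changes one assumption from Step 4.

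| Change | Power |
|---|---|
| Divisor 6 (systolic and diastolic both primary, as under Primary endpoint) | 68% |
| All 107 analysed, 15% carried forward at zero change (difference 8 × 0.85 = 6.8) | 68% |
| Divisor 2 | 81% |
| All 107 analysed, effects undiluted | 83% |
| SD 20 unadjusted, assumed baseline correlation 0.5 (residual SD 20 × √(1 − 0.25) = 17.3) | 88% at 91, 89% at 93 |

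**Step 6: effect of the multiplicity method.** Simulation of the three tests at 91 per group, Step 4 assumptions, gives for pooled v sham: Bonferroni 76%, Holm 81%, fixed sequence in the listed order at 5% each 87%.

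**The case against.** The best defence is that nothing is wrong with the analysis itself. Bonferroni is valid and prespecified, and the type I error is controlled. An unadjusted 88% against sham is near enough to 90%, and against waiting list 93 is more than the calculation needs. The ANCOVA may also recover power, and intention-to-treat with carry-forward keeps all 107 patients per group, not 91. Much of this stands. The failure to reproduce 93 is of little consequence for the sham contrast taken alone, and the 76% is conditional.

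Two stronger readings are tempting and are not supported. A reader might infer that the trial has a one-in-four chance of missing the assumed effect against sham. The article does not give the divisor, the meaning of the SD or the effect of carry-forward, so 76% is one point in a range of about 68% to 89%. A reader might also infer that pooled acupuncture versus waiting list is safe at 97%. The Abstract counts sham among the three acupuncture groups, and pooling it too would give 85%.

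What the defence cannot do is restore the 90%. One variant comes close to 93: an equal-sized t-test of 11 mmHg at 0.05/3 needs 91. But it uses neither the stated 5% level nor the planned 2:1 contrast. Even the most favourable reading for sham, which needs a baseline correlation that the article does not state, stays just under 90%. No reading considered here rescues AMA v NMA.

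**Conclusion.** The point holds. The stated combination of 93 per group, 90% power and a 5% level does not describe any of the planned comparisons, and the level used for sizing conflicts with the correction used for analysis. For pooled verum versus sham the unadjusted gap is small (88% against 90%), and the material loss comes from Bonferroni. Power is about 76% if the divisor is 3, SD 20 is the residual SD and 91 per group are evaluable, with a range of about 68% to 89% under other readings. The weakest comparison is AMA v NMA: about 4% at 0.0167 and 10% at 5% for the assumed 2 mmHg.

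This is an error in the stated power. It does not make the analysis invalid, and it does not show that the trial must be enlarged.

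**What to change.** 1. Replace the single 90% with power for each of the three planned comparisons at the alpha actually used. State the Bonferroni or other divisor, what SD 20 refers to, how many patients per group are assumed to be analysed, and whether sham is pooled in the waiting-list comparison.
2. Say plainly that AMA v NMA is not powered for the assumed 2 mmHg difference.
3. Replace Bonferroni with Holm on the same three tests. Holm controls the family-wise error at 5%, is never less powerful than Bonferroni, and lifts pooled v sham from about 76% to 81% under the assumptions above.
4. Optionally, test in the order already listed, each at two-sided 5%, which gives about 87% for sham. This is a trade-off, because later comparisons lose confirmatory status if an earlier one fails.

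The cost is a less favourable stated power and an amendment to the multiplicity rule. With 184 of 428 patients recruited according to Trial status, the amendment should be dated and made before any outcome data are compared between arms. No extra enrolment is needed.

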**Methods/Design:**

This is a large scale, open-label, multicenter, randomized controlled clinical trial with four parallel arms. We will recruit 428 hypertensive patients with systolic blood pressure (SBP) between 140 and 159 mmHg, diastolic blood pressure (DBP) between 90 and 99 mmHg. The participants will be randomly assigned to four different groups (three acupuncture groups and one waiting list group) (1).The affected meridian acupuncture group (*n* = 107) is treated with acupoints on the affected meridians (2).The non-affected meridian acupuncture group (*n* = 107) is treated with acupoints on the non-affected meridians (3).The invasive sham acupuncture group (*n* = 107) is provided with sham acupoints treatment (4).The waiting-list group (*n* = 107) is not offered any intervention until they complete the trial. Each patient allocated to acupuncture groups will receive 18 sessions of acupuncture treatment over 6 weeks. This trial will be conducted in 11 hospitals in China. The primary endpoint is the change in average 24-hSBP before and 6 weeks after randomization. The secondary endpoints are average SBP and average DBP during the daytime and night-time, and 36-Item Short Form Survey (SF-36), and so on.

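### Enrolling 107 per group does not keep the required 93 at the protocol's own 15% drop-out rate: about 91 remain (minor; about one point of power)

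*Protocol article*

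**What the plan says.** All references are to the protocol article. Under *Sample size calculation and statistical analysis*, the calculation is described as follows: "We calculated this using 90% power at a 5% significance level with G*Power", and "the result showed an estimated 93 patients per group". The inputs are the expected falls in average 24-h systolic pressure ("we anticipated an 12 mmHg improvement by affected meridian acupuncture; 10 mmHg by non-affected meridian acupuncture; 3 mmHg by sham acupuncture; and 0 mmHg", where the last value is for patients on the waiting list) and the spread ("The standard deviation is set as 20"). The enrolment target follows: "Considering a drop-out rate of 15%, we plan to enroll 107 patients per group", which makes a total of 428 over the four arms. The Abstract repeats the total ("We will recruit 428 hypertensive patients"), and Table 1 repeats 107 for each arm. Allocation is equal across the arms (Randomization: "each eligible patient having an equal probability of being assigned to four different groups").

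Three other statements bear on the point:
- The primary endpoint is the change from before randomization to week 6 (*Primary endpoint*), while follow-up continues to week 12 (*Design*).
- Ambulatory monitoring takes place at baseline and at weeks 6, 9 and 12 (*Blood pressure measurement*).
- Analyses use both an intention-to-treat and a per-protocol population, and missing values are filled by last observation carried forward (*Sample size calculation and statistical analysis*).

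The article does not write out the formula for the drop-out allowance, and it does not say over what period the 15% is expected.

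**The concern.** A drop-out rate is a share of the patients enrolled. If N are enrolled and a share d is lost, N × (1 − d) remain, so the number to enrol is the required number divided by (1 − d). Multiplying the required number by (1 + d) always gives too few. The planned 107 looks like the product of that multiplication.

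What is at stake is whether the recruitment target delivers the number that the protocol says it needs, under the loss that it assumes. Because the section inflates 93 to allow for drop-out, it treats 93 as the number wanted after losses. The requirement, the loss rate and the target are all stated, so this is not a detail left to an analysis plan.

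**Working it through.** **Inputs** (*Sample size calculation and statistical analysis*): required number 93 per group; drop-out 15%; enrolment 107 per group, 428 in total.

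**1. Reproducing the plan's figure.** 93 × (1 + 0.15) = 106.95, rounded up to 107; 4 × 107 = 428. Both stated figures are matched exactly.

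**2. The number needed to keep 93.** 93 / (1 − 0.15) = 109.41, rounded up to 110. Check: 110 × 0.85 = 93.5. Total 4 × 110 = 440, which is 3 more per group and 12 more overall than planned.

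**3. What 107 delivers.** 107 × 0.85 = 90.95, about 91 per group. That is 2 short of 93 per group and 8 short over four groups.

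**4. The loss that 107 can absorb.** 1 − 93/107 = 14/107 = 13.1%.

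Steps 2 to 4 do not depend on how the plan arrived at 107.

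**5. The cost in power.** One named comparison serves as an example: the two active arms pooled against sham. The expected difference is (12 + 10)/2 − 3 = 8 mmHg, with SD 20 and a 2:1 ratio (2n pooled, n sham), using a two-sided t-test. The article does not state the number of sides, so two-sided is an assumption. The noncentrality is 8 / (20 × √(1/(2n) + 1/n)), which is 3.150 at n = 93 and 3.116 at n = 91.

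| Alpha | n = 93 | n = 91 |
|---|---|---|
| 0.05 | 88.1% | 87.4% |
| 0.0167 (= 0.05/3) | 77.0% | 76.0% |

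The second row assumes that the Bonferroni correction covers the three primary comparisons listed in the analysis text.

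Simple two-arm comparisons (two-sided 5%, SD 20) give the same picture:

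| Difference | n = 93 per arm | n = 91 per arm |
|---|---|---|
| 7 mmHg | 66.1% | 65.1% |
| 9 mmHg | 86.3% | 85.5% |
| 10 mmHg | 92.4% | 91.8% |

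In every case the loss is about one percentage point or less.

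**The case against.** The strongest reply is that the intention-to-treat analysis with last observation carried forward loses nobody. A baseline 24-h recording exists, so a patient who leaves before week 6 has a value to carry and stays in the set. A reader might infer from the arithmetic that the intention-to-treat analysis shrinks to 91. The article does not support that: the intention-to-treat count remains 107, and 91 describes completers or roughly the per-protocol set. What survives is that no ambulatory recording is scheduled between baseline and week 6. A patient lost in that interval therefore carries the baseline forward, contributes a change of zero, and adds no observed week-6 outcome.

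Second, the 15% has no stated period. If it covers all 12 weeks after randomization, patients lost after week 6 still supply the primary endpoint. Since 107 tolerates 13.1% loss by week 6, 93 would still be met if about 2 of the 15 percentage points (15 − 13.1 = 1.9) fell later. This stands as a condition on the finding. The article does not say which reading applies.

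Third, the multiplication by 1.15 is an inference. The exact match makes it likely, but it is not documented. The mismatch between 93, 15% and 107 holds without it.

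Fourth, the gap is too small to affect any conclusion. That is fair as to size and is why the point is minor. It does not make the stated figures consistent.

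**Conclusion.** Wrong as written, and minor. At the protocol's own drop-out rate, 107 per group leaves about 91 patients with an observed outcome, not 93. Keeping 93 would take 110 per group. The finding takes 93 and 15% as given and assumes that the whole 15% is lost before the week-6 endpoint. It concerns completers or the per-protocol set.

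A reader might also infer that this slip explains why power in the example above falls below the stated 90%. It does not. At 93 per group the pooled comparison with sham already stands at 88.1%, or 77.0% at the adjusted alpha, and the drop-out allowance adds only about one point to the gap. Whether 93 follows from the stated effect sizes and SD is a separate question that this point does not settle.

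**What to change.** Keep enrolment at 428. With 184 participants already recruited (*Trial status*) and about one point of power in question, a new target is not warranted by this point alone. Replace the drop-out sentence with one that says:

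- 107 per group yields 93 completers only if drop-out by week 6 is at most 13%, and about 91 if it is 15%;
- the period to which the 15% applies;
- the power at 91 per group for a named comparison, difference, SD, allocation ratio and alpha. For pooled active against sham (8 mmHg, SD 20, 2:1) this is 87.4% at two-sided 0.05, or 76.0% at 0.0167 if the Bonferroni correction covers three comparisons.

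The cost is a change of wording and a less favourable power statement. Almost all of the distance from 90% in that statement would come from sources other than the drop-out allowance, and the text should not attribute it to drop-out. No enrolment, visit or procedure changes.
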